##### Predictors of Treatment Response

Baseline levels of sleep reactivity and pandemic-related risk factors, including loneliness, perceived stress, screen time, social connection, and physical activity, are measured as predictors of long-term treatment outcomes.

Loneliness is measured using the University of California, Los Angeles (UCLA) Loneliness Scale [49]. This self-report measure assesses participant's subjective feelings of loneliness and social isolation. The UCLA Loneliness Scale asks participants to rate how often each of the 20 items is descriptive of them, rated from 1 (never) to 4 (often). The responses are for an overall score range of 20 to 80, with higher scores indicating greater degrees of reported loneliness.

Sleep reactivity is measured by the Ford Insomnia Response to Stress Test (FIRST) [50]. This 9-item self-report tool measures risk of participants experiencing situational insomnia due to common stressful conditions. A higher score on the FIRST indicates higher sleep reactivity. The FIRST has good reliability and validity and has demonstrated high internal consistency across multiple demographic groups in clinical and population-based samples [51].

Perceived stress is measured using the Perceived Stress Scale (PSS) [52]. The PSS is a widely used 14-item self-report questionnaire that assesses how stressful participants believe their lives to be. Items are generalized and measure the degree to which participants judge their lives to have been uncontrollable and unpredictable over the course of the previous month. Items are scored on a 5-point Likert scale, with total scores ranging from 0 to 56 and higher scores indicating higher levels of perceived stress.

Screen time is measured through modified self-report questions in the Coronavirus Health Impact Survey (CRISIS) [53]. Participants are asked to estimate the number of hours spent per day, over the course of the 2 most recent weeks, watching television or digital media (eg. Netflix, YouTube, web surfing) or using social media (eg. FaceTime, Facebook, Instagram, Snapchat, Twitter, TikTok).

Social connection is measured by the Social Network Index (SNI) [54]. The SNI is a 12-item questionnaire that assesses participation in different types of social relationships. The 12 types of relationships (eg, friend, children, spouse, religious group member) are scored by the number of network members with which they communicate at least every 2 weeks. A higher score on the SNI indicates a larger social network.

Physical activity is evaluated using the International Physical Activity Questionnaire (IPAQ) [55]. The IPAQ assesses the time spent on an individual's physical activity across 5 life domains over the previous 7 days. The activity domains consist of physical activity related to work, transportation, housework and caring for family, and recreation and sports, as well as the amount of time spent sitting each day. Minutes of sitting and walking, as well as moderate-intensity (walking not included) and vigorous-intensity activities, were calculated for each domain and for the entire past 7 days. The IPAQ has high reliability and validity and has been widely used to measure comparable estimates of physical activity in large populations. A higher score on the IPAQ indicates an increased physical activity.

#### Secondary Outcomes

All secondary outcomes of insomnia and well-being are collected at weeks 0, 12, 28, and 56. Secondary measures of insomnia and the Generalized Anxiety Disorder-7 (GAD-7) are also collected at weeks 1-6.

##### Insomnia

Changes in sleep onset latency (SOL), number of awakenings, wake after sleep onset (WASO), total sleep time (TST), and sleep efficiency (SE) over time are measured as secondary measures of insomnia symptoms using sleep diaries; 7 days of sleep diaries are collected at baseline and weeks 1-5, 12, 28, and 56. Sleep diaries collect information about sleep and rise times, time in and out of bed, number of middle-of-the-night awakenings, duration of these awakenings, sleep quality, nap frequency and duration, and caffeine and alcohol consumption. SOL is the time in minutes from “lights out” to sleep onset. WASO is the sum of the total number of minutes of wakefulness occurring after sleep onset and before final awakening (sleep offset). TST is the total time spent asleep, from the start of sleep onset to sleep offset, subtracting any periods of wakefulness. SE is calculated as TST divided by total time spent in bed, multiplied by 100.

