### Objectives

Our feasibility, pilot study investigates the viability of an early treatment for insomnia symptoms to treat insomnia symptoms arising during the COVID-19 pandemic and determine pandemic-related risk factors for worsening well-being and sleep outcomes. We also assess the impact of the intervention on insomnia severity and well-being across 28 weeks.

We will accomplish these objectives by conducting a waitlist-controlled trial across 28 weeks to address 3 aims.

Aim 1 is to determine whether a brief, telehealth CBT-I reduces insomnia symptoms arising during the COVID-19 pandemic. We hypothesize that CBT-I will lead to improvements in insomnia severity, as measured by the Insomnia Severity Index (ISI) [35,36], across 28 weeks. We also hypothesize that fewer participants in the CBT-I group will meet the Diagnostic and Statistical Manual of Mental Disorders 5th Edition (DSM-5) criteria for insomnia disorder, compared with the waitlist control group at weeks 12 and 28.

Aim 2 is to determine whether brief, telehealth CBT-I mitigates negative mental health outcomes arising during the COVID-19 pandemic. We hypothesize that, compared with the waitlist control group, the CBT-I group will have an improved trajectory of well-being across 28 weeks and will have better well-being at weeks 7, 12, and 28. Additionally, we hypothesize improvements in insomnia symptoms will mediate improvements in well-being from baseline to weeks 6, 12, and 28.

Aim 3 is to determine whether risk factors for insomnia that might be aggravated during the COVID-19 pandemic predict worse insomnia and negative mental health outcomes at follow-up. We hypothesize that self-reported high levels of social isolation, perceived stress, sleep reactivity, and screen time and low physical activity at baseline will predict worse long-term outcomes at 12 and 28 weeks across both study groups.

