## Methods

### Trial Design

#### Overall Design

We designed a 2-arm randomized controlled feasibility trial to investigate the efficacy of an early, brief, telehealth-delivered insomnia treatment to prevent adverse sleep and well-being outcomes. Participants with clinically significant insomnia symptoms (current ISI total score ≥10) that began during the pandemic were randomized to either a treatment group or a waitlist control group. Treatment consists of 4 telehealth sessions of CBT-I delivered over 5 weeks. Participants in the waitlist control group do not receive any study interventions during the 28-week primary assessment period. All participants complete assessments of insomnia symptom severity, depressive symptom severity, anxiety symptom severity, quality of life, and pandemic-related risk factors at baseline (week 0), weeks 1-6, week 12, week 28, and week 56 (Figure 1). Primary outcomes focus on weeks 6, 12, and 28.

This study design creates 2 study phases: a 28-week waitlist-controlled (primary assessment) period, which allows the assessment of the therapy compared with a treatment-naive group and a delayed-start (secondary assessment) period, during which participants originally assigned to the waitlist control group receive the study therapy and participants assigned to the treatment group no longer receive study treatment (Figure 2). This allows assessment of long-term changes in sleep and well-being between individuals who underwent an early behavioral intervention for insomnia and those who did not. Our innovative approach will help elucidate mechanistic pathways between sleep and well-being as well as provide a needed clinical response to the COVID-19 pandemic and resulting mental health crisis.

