#### Primary Analyses

Statistical analyses aim 1 is to determine whether a brief, telehealth CBT-I reduces insomnia symptoms arising during the COVID-19 pandemic. All primary analyses will be performed using the intention-to-treat principle. We will test whether CBT-I is superior to a waitlist control in reducing insomnia symptoms by using a mixed effects linear model with autoregressive error structure using intention-to-treat analysis with outcomes at time points 6, 12, and 28. Insomnia severity as measured by the ISI will be entered as the dependent variable with randomization group (2 levels), time point (weeks 0, 6, 12, and 28), and group-by-time interaction included as fixed effects. The model will also include a random slope. Several hypotheses (1.1a-d) will be tested using the described mixed effects model.

Hypothesis 1.1a is that individuals assigned to the CBT-I group will experience an improved trajectory of insomnia symptoms during the waitlist-controlled 28-week period relative to those assigned to the waitlist control group. This hypothesis will be tested using a likelihood ratio test of the coefficients of the time and group-by-time interaction of the aforementioned mixed effects linear model.

Hypotheses 1.1b-1.1d are that individuals assigned to the CBT-I group during the waitlist-controlled period will have lower insomnia symptoms compared with those assigned to the waitlist-control group immediately posttreatment (hypothesis 1.1b; week 6) and at the short-term (hypothesis 1.1c; week 12) and long-term (hypothesis 1.1d; week 28) follow-ups. These hypotheses will be tested using the aforementioned mixed effects linear model with independent likelihood ratio tests using the treatment coefficient for the posttreatment (hypothesis 1.1b; Δ_1_ in Figure 2), short-term (hypothesis 1.1c; Δ_2_ in Figure 2), and long-term (hypothesis 1.1c; Δ_3_ in Figure 2) follow-up time points.

We will also test whether CBT-I is superior to the waitlist control in preventing an insomnia diagnosis following treatment by using multiple logistic regression analysis.

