#### Secondary Analyses

Secondary analyses will be conducted. (1) Analytic methods described in the primary aims will be repeated but applied to secondary measures of sleep disturbance and well-being outcomes as described in the Secondary Outcomes section. (2) Analytic methods described in the primary aims will be repeated but applied to outcome measures collected at week 56. (3) Sparse unsupervised clustering and principal component analysis analyses will be used to identify cohesive factors of dysfunction in sleep complaints and patterns of mental health outcomes at baseline. Regression models will be used to quantify the relationships within and between sleep complaints and patterns of mental health outcomes. (4) Age and sex differences in treatment response and as moderators of relationships between sleep complaints, insomnia risk factors, and mental health outcomes will be explored.

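### The outcome schedule contradicts itself on week 6, and four secondary well-being scales have no week 6 value for the posttreatment contrast carried over to them

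*Protocol article*

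**What the plan says.** **Diary.** Sleep onset latency, number of awakenings, wake after sleep onset, total sleep time and sleep efficiency "are measured as secondary measures of insomnia symptoms using sleep diaries". Two statements give their schedule:

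- Secondary Outcomes, opening paragraph: "Secondary measures of insomnia and the Generalized Anxiety Disorder-7 (GAD-7) are also collected at weeks 1-6".
- Secondary Outcomes, Insomnia: "7 days of sleep diaries are collected at baseline and weeks 1-5, 12, 28, and 56".

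**Secondary well-being scales.** The opening of Secondary Outcomes sets the general rule: "All secondary outcomes of insomnia and well-being are collected at weeks 0, 12, 28, and 56". It adds weeks 1-6 for only one well-being scale, the GAD-7. That leaves S-STS, SF-36, BAI and BDI-II at weeks 0, 12, 28 and 56.

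**Overall Design.** "All participants complete assessments of insomnia symptom severity, depressive symptom severity, anxiety symptom severity, quality of life, and pandemic-related risk factors at baseline", and the sentence goes on to weeks 1-6, 12, 28 and 56.

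**Analyses.** The Aim 1 mixed model is specified "using intention-to-treat analysis with outcomes at time points 6, 12, and 28". The Aim 2 model uses weeks 0-6, 12 and 28, names the BDI-II as dependent variable, and includes a week 6 posttreatment hypothesis (2.2b). The Aim 2 text extends the work to the secondary well-being measures, giving anxiety, suicidality and quality of life as examples. Secondary Analyses, item 1, adds: "Analytic methods described in the primary aims will be repeated but applied to secondary measures of sleep disturbance and well-being outcomes".

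**Aim 2 in Objectives.** The CBT-I group "will have better well-being at weeks 7, 12, and 28".

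**The concern.** A posttreatment contrast needs an observation at the posttreatment visit, which Data Collection places at week 6. For some secondary measures the stated schedule has none. For others, two statements disagree on whether it exists. An analyst following the article could not tell which outcomes belong in the week 6 comparison. A reader of the results could not tell whether a missing week 6 estimate reflects the design, lost data or selective reporting.

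The conflict also touches the Aim 2 primary model. Its named dependent variable, the BDI-II, is a secondary measure that Secondary Outcomes does not schedule at any of weeks 1-6. The Well-being subsection of Primary Outcomes names the PHQ-9 as the primary depression measure, and the PHQ-9 does have those weeks.

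**Working it through.** The plan's only design figure, 80% power with 25 per group at d = 0.80, concerns week 28. It reproduces (80.7% by normal approximation, 79.1% by the exact t test) and does not bear on this point. The check here compares schedules.

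**Inputs.**

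- Weeks tested in the primary-aim methods: {6, 12, 28} (Primary Analyses, hypotheses 1.1b-d and 2.2b-d).
- Weeks in the Aim 1 model, which the diary variables would inherit: {0, 6, 12, 28}.
- Weeks in the Aim 2 model, which the well-being scales would inherit: {0, 1, 2, 3, 4, 5, 6, 12, 28}.
- Collection weeks for each measure, as stated in the sections named below.

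**Rule.** Missing weeks = weeks required minus weeks collected.

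| Measure and source of schedule | Weeks collected | Missing from tested weeks | Missing from model weeks |
|---|---|---|---|
| Diary, opening of Secondary Outcomes | 0, 1-6, 12, 28, 56 | none | none |
| Diary, Insomnia subsection | 0, 1-5, 12, 28, 56 | 6 | 6 |
| GAD-7, opening of Secondary Outcomes | 0, 1-6, 12, 28, 56 | none | none |
| S-STS, BAI, BDI-II, opening of Secondary Outcomes | 0, 12, 28, 56 | 6 | 1-6 |
| SF-36, opening of Secondary Outcomes | 0, 12, 28, 56 | 6 | 1-6 |
| SF-36, Overall Design | 0, 1-6, 12, 28, 56 | none | none |

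**Count.** There are 5 diary variables and 5 secondary well-being scales, so 10 secondary outcomes.

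- On the opening paragraph of Secondary Outcomes alone, 4 of the 5 well-being scales lack week 6 and the diary does not: 4 of 10.
- If the Insomnia subsection is right about the diary, 4 + 5 = 9 of 10 lack it.
- If Overall Design is right about SF-36 and the diary was collected at week 6, 4 - 1 = 3 of 10 lack it.

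**How far Overall Design conflicts.** It lists domains, not scales. The PHQ-9 and GAD-7 can satisfy it for depression and anxiety, so BDI-II and BAI need not have been given weekly. Suicidality is not in its list. SF-36 is the only quality-of-life scale, so for that domain the two sections cannot both be right.

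**Week 7.** Overall Design, Control Condition, Primary Outcomes and hypothesis 2.2b all use week 6, and no schedule contains week 7. The mediation sentence that follows in Aim 2 uses weeks 6, 12 and 28.

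**The case against.** The strongest reply is that Secondary Analyses repeats methods, and does not promise every time point for every scale. The article already adapts one contrast to its schedule: the Duke insomnia diagnosis is collected at weeks 0, 12, 28 and 56 and tested only at weeks 12 and 28. On that view S-STS, SF-36 and BAI would be tested at weeks 12 and 28, with the details left to an analysis plan. The measures are also secondary in a feasibility trial that emphasises estimation, ISI and PHQ-9 do have week 6 data, and week 7 is an evident slip.

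Part of this stands. The Duke example shows that a restricted contrast is workable, and the matter is modest in weight. But for the Duke the article states the restriction. For the secondary well-being measures it points to the Aim 2 model with its weeks 0-6 and its week 6 hypothesis, and restricts nothing. An analysis plan could choose contrasts, but it would not remove two incompatible collection schedules from this document.

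Two stronger readings are tempting and are not supported:

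- A reader might infer that no week 6 diary exists, so the diary contrast cannot be run. That follows only if the Insomnia subsection governs. The opening of the same section says the opposite, and nothing in the article settles it.
- A reader might infer that the week 5 diary would stand in for posttreatment, with sleep efficiency inflated by restricted time in bed. The article plans no such substitution. Table 1 puts Session 4 in week 4 or 5, so a week 5 diary may follow the last session for some participants. Time-in-bed restriction is also part of the assigned treatment, and could still be in force at week 6.

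**Conclusion.** The point holds as an inconsistency in the outcome schedule, and between that schedule and the analyses that rely on it. On the Secondary Outcomes schedule, S-STS, SF-36, BAI and BDI-II have no week 6 value, so the week 6 contrast carried over to them has no observed data. Whether the five diary variables share that gap is undetermined. Depending on which statements are right, between 3 and 9 of the 10 secondary outcomes lack week 6. The lower figure assumes that the domain list in Overall Design does not imply weekly BAI or BDI-II. No bias in any estimate is shown. The consequence is an analysis that is partly undefined as written. It should be corrected but does not threaten the ISI or PHQ-9 comparisons.

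**What to change.** 1. Check which measures were actually collected at week 6, and bring Overall Design, the opening of Secondary Outcomes and the Insomnia subsection into line with that record.
2. Limit the week 6 secondary contrast to measures with week 6 data: the GAD-7, and the diary variables only if the diary was collected at week 6. Restricting the diary to weeks 12 and 28 before checking could discard valid data.
3. For S-STS, SF-36, BAI and BDI-II, state contrasts at weeks 12 and 28 only and model time points 0, 12 and 28. If the record shows SF-36 was given at week 6, it joins the first group.
4. In the Aim 2 model, reconcile the BDI-II as dependent variable over weeks 0-6 with its collection schedule and with the PHQ-9 as the named primary measure.
5. In Aim 2 of Objectives, change week 7 to week 6.

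The cost is wording only. Enrollment closed in June 2021 and only week 28 and week 56 data were outstanding in October 2021, so absent week 6 data cannot be added. The price is that no posttreatment contrast is claimed for measures not collected at week 6.

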##### Well-being

Secondary measures of well-being include measures of anxiety symptoms, suicidal ideation, and quality of life, as well as an additional measure of depressive symptoms.

Anxiety symptoms over time are assessed using the GAD-7 [56]. The GAD-7 is a widely used diagnostic self-report scale that assesses severity of anxiety symptomology. The GAD-7 is a 7-item, 4-point Likert scale ranging from 0 to 3 that measures severity of anxiety symptoms over the previous 2 weeks, with a total score ranging from 0 to 21. Higher scores indicate more severe anxiety symptomology.

Suicidal ideation and behaviors over time are measured by the S-STS [47]. For this outcome measure, 14 items (excluding item 15) are summed for an overall score ranging from 0 to 56. Again, higher scores indicate more severe difficulties.

Quality of life is assessed using the 36-Item Short Form Health Survey (SF-36) [57]. The SF-36 is a 36-item self-report survey to assess comprehensive quality-of-life measures. It consists of 8 subscales: vitality, physical functioning, bodily pain, general health perceptions, physical role functioning, emotional role functioning, and mental health. This survey is widely used and has been proven to be a reliable indicator of quality-of-life measures. The global score range is 0 to 100, with higher scores indicating better health conditions.

The Beck Anxiety Inventory (BAI) [58] is used as a measure of anxiety symptom change over time. The BAI is a 21-item self-report scale that assesses the severity of anxiety symptoms. Items are scored from 0 to 3. Higher scores indicate greater levels of severity, and the ranges for anxiety levels are as follows: 0-9, normal to minimal; 10-18, mild to moderate; 19-29, moderate to severe; and 30-63, severe. The BAI consists of 2 factors: somatic and cognitive.

The Beck Depression Inventory-II (BDI-II) [59,60] is used as a secondary measure of depressive symptom change over time. We will sum all items except one sleep item, and the average item score for the remaining 20 items will be multiplied by 21 (the original number of items) to create a modified depression scale that maintains the original range (ranges: 0-13, minimal; 14-19, mild; 20-28, moderate; and 29-63, severe). The BDI-II is a 21-item self-report scale with high validity and reliability that assesses the severity of depressive symptoms. The depressive items consist of sadness, pessimism, past failure, loss of pleasure, guilty feelings, punishment feelings, self-dislike, self-criticalness, suicidal thoughts or wishes, crying, agitation, loss of interest, indecision, worthlessness, loss of energy, changes in sleep pattern, irritability, changes in appetite, concentration difficulty, tiredness or fatigue, and loss of interest in sex. Items are scored from 0 to 3, and higher scores indicate greater level of severity.

### Statistical Procedure and Data Analysis

Given the nature of this feasibility study, for all our analyses and interpretation, we will place a primary emphasis on estimation of effect sizes and confidence intervals rather than on testing statistical significance.

#### Primary Analyses

Statistical analyses aim 1 is to determine whether a brief, telehealth CBT-I reduces insomnia symptoms arising during the COVID-19 pandemic. All primary analyses will be performed using the intention-to-treat principle. We will test whether CBT-I is superior to a waitlist control in reducing insomnia symptoms by using a mixed effects linear model with autoregressive error structure using intention-to-treat analysis with outcomes at time points 6, 12, and 28. Insomnia severity as measured by the ISI will be entered as the dependent variable with randomization group (2 levels), time point (weeks 0, 6, 12, and 28), and group-by-time interaction included as fixed effects. The model will also include a random slope. Several hypotheses (1.1a-d) will be tested using the described mixed effects model.

Hypothesis 1.1a is that individuals assigned to the CBT-I group will experience an improved trajectory of insomnia symptoms during the waitlist-controlled 28-week period relative to those assigned to the waitlist control group. This hypothesis will be tested using a likelihood ratio test of the coefficients of the time and group-by-time interaction of the aforementioned mixed effects linear model.

Hypotheses 1.1b-1.1d are that individuals assigned to the CBT-I group during the waitlist-controlled period will have lower insomnia symptoms compared with those assigned to the waitlist-control group immediately posttreatment (hypothesis 1.1b; week 6) and at the short-term (hypothesis 1.1c; week 12) and long-term (hypothesis 1.1d; week 28) follow-ups. These hypotheses will be tested using the aforementioned mixed effects linear model with independent likelihood ratio tests using the treatment coefficient for the posttreatment (hypothesis 1.1b; Δ_1_ in Figure 2), short-term (hypothesis 1.1c; Δ_2_ in Figure 2), and long-term (hypothesis 1.1c; Δ_3_ in Figure 2) follow-up time points.

We will also test whether CBT-I is superior to the waitlist control in preventing an insomnia diagnosis following treatment by using multiple logistic regression analysis.

Hypotheses 1.2a and 1.2b are that individuals who were assigned to the CBT-I group will be less likely to have an insomnia diagnosis than those who were assigned to the waitlist control group at weeks 12 and 28. These hypotheses will be tested using 2 separate logistic regression models, one using the short-term (hypothesis 1.2a; 12 weeks) and one using long-term (hypothesis 1.2b; 28 weeks) follow-up insomnia diagnosis, as defined by the Duke, as the dependent variable, with treatment (CBT-I, waitlist) as the independent variable.

Statistical analyses aim 2 is to determine whether a brief, telehealth CBT-I improves well-being during the COVID-19 pandemic. We will test whether immediate CBT-I is superior to a waitlist control in improving depressive symptoms as the primary measure of well-being during the waitlist-controlled period (28-week duration) by using a mixed effects linear model with autoregressive error structure using intention-to-treat analysis. Depression severity, as assessed by the BDI-II, will be entered as the dependent variable with baseline covariates used for stratified randomization (ie, baseline insomnia severity and sex), group (immediate CBT-I or waitlist control), time point (weeks 0-6, 12, and 28), and group-by-time interaction included as fixed effects. The model will also include a random slope. Separate, secondary analyses will be conducted on the secondary measures relating to well-being described in the Secondary Outcomes section (eg, anxiety, suicidality, quality of life). Several hypotheses will be tested using this model.

Hypothesis 2.2a is that individuals assigned to the CBT-I group will have an improved trajectory of depressive symptoms across the 28 weeks relative to individuals assigned to the waitlist control group. This hypothesis will be tested using a likelihood ratio test of the coefficients of the time and group-by-time interaction terms of the aforementioned mixed effects linear model.

Hypotheses 2.2b-2.2d are that individuals assigned to the CBT-I group will have lower depressive symptoms compared who those who were assigned to the waitlist control group immediately posttreatment (hypothesis 2.2b; week 6) and at the short-term (hypothesis 2.2c; week 12) and long-term (hypothesis 2.2d; week 28) follow-ups. These hypotheses will be tested using the aforementioned mixed effects linear model with independent likelihood ratio tests using the treatment coefficient for the posttreatment (hypothesis 1.2b; week 6), short-term (hypothesis 1.2c; week 12), and long-term (hypothesis 1.2c; week 28) follow-up time points.

Hypothesis 2.3 is that improvement in insomnia symptom severity (measured by the ISI) will mediate subsequent improvement in well-being from baseline (week 0) to posttreatment (week 6), short-term follow-up (week 12), and long-term follow-up (week 28). Using the approach described by Kraemer at al [61] and Manber et al [34], linear regression analyses will be used to determine whether change in the ISI score from Session 1 (week 1) to Session 4 (week 5) of treatment mediates the subsequent depressive symptom improvement (primary outcome measure) after the completion of treatment (week 6). Change in ISI score at Session 4 will be estimated as the slope of the regression line of ISI scores from Session 1 (week 1) through the treatment phase to Session 4 (week 6) using all available data from each participant. The model will include group (CBT-I or waitlist control), change in ISI score from Session 1 to Session 4 (participant specific slopes), and their interaction with depression severity, as measured by the PHQ-9, as the dependent variables. Mediation will be tested using the MacArthur approach as described by Kraemer et al [62]. Specifically, a mediation effect requires a significant effect of the intervention on the mediator (Path A in Figure 3) and a significant association between the mediator and the outcome (Path B in Figure 3).

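### Hypotheses 1.1a and 2.2a compare the arms, but their test also includes the time coefficients, so improvement shared by both arms could be read as a CBT-I effect

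*Protocol article*

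**What the plan says.** All of this is in the Protocol article, Primary Analyses.

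- **Hypothesis 1.1a** is relative. CBT-I participants are to show an "improved trajectory of insomnia symptoms during the waitlist-controlled 28-week period relative to those assigned to the waitlist control group".
- **The aim 1 model** for the ISI lists "randomization group (2 levels), time point (weeks 0, 6, 12, and 28), and group-by-time interaction included as fixed effects". The time main effect and the interaction are thus separate terms.
- **The test of 1.1a** is given in one sentence, as "a likelihood ratio test of the coefficients of the time and group-by-time interaction of the aforementioned mixed effects linear model".
- **Hypothesis 2.2a** is also relative: an "improved trajectory of depressive symptoms across the 28 weeks relative to individuals assigned to the waitlist control group". Its test is again a "likelihood ratio test of the coefficients of the time and group-by-time interaction terms", from a model whose time points are weeks 0-6, 12 and 28.

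Hypotheses 1.1b-d and 2.2b-d use the treatment coefficient at weeks 6, 12 and 28. The opening of Statistical Procedure and Data Analysis ranks effect sizes and confidence intervals above significance tests.

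**The concern.** Only the group-by-time coefficients say whether the arms follow different courses. With waitlist as the reference level, the time coefficients are the waitlist arm's own change from baseline. If both sets are dropped from the reduced model, the null becomes flat trajectories in both arms. If both arms improve equally, that null is false and the test should reject, yet the hypothesis of a relative benefit is also false.

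Shared improvement is plausible for the ISI. Entry requires a current score of at least 10 (Recruitment, Enrollment Criteria, Screening, and Retention). Screening data serve as baseline, and week 0 is a time point in the model. Selecting on a threshold and reusing the same score as the first outcome value invites regression to the mean in both arms. For depression a shared fall is possible, but the argument is less direct because there is no minimum depression score at entry.

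At stake is a significant result for 1.1a or 2.2a, reported as a better course under CBT-I, that reflects only the passage of time.

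**Working it through.** **1. The plan's own figure.** The only design figure is 80% power at d = 0.80 with 25 per group, two-group t test at week 28, 5% level (Power Calculation; two-sided assumed). Normal approximation: 0.80 × √(25/2) = 2.828, and Φ(2.828 − 1.960) = Φ(0.868) = 80.7%. The exact t test gives 79.1%. The figure reproduces. It concerns the week-28 difference; no error rate or power is stated for the trajectory tests.

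**2. Degrees of freedom, time as a factor.**
- Aim 1, four visits: 3 time + 3 interaction. The joint test has 6 df (5% critical value 12.59); interaction only has 3 df (7.81).
- Aim 2, nine visits as listed: 8 + 8. The joint test has 16 df (26.30); interaction only has 8 df (15.51).

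**3. Assumptions, since the documents give no values.** No treatment effect; both arms fall by δ SD at every visit after baseline; equal variance at all visits; complete data; 25 per arm; within-person correlation ρ of 0.3, 0.5 or 0.7, either exchangeable or first-order autoregressive by visit; no random slope.

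**4. Formula.** The large-sample statistic is noncentral chi-square. With N = 50 in total, mean profile μ = (0, −δ, …, −δ) and correlation matrix V,

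λ = N × [μ′V⁻¹μ − (1′V⁻¹μ)² / (1′V⁻¹1)].

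Under exchangeable correlation with T visits this becomes λ = N δ² (T − 1) / [T(1 − ρ)]. For the interaction-only test λ = 0 whatever δ is, because the arms have the same profile.

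Example, aim 1, δ = 0.5, ρ = 0.5, exchangeable: 50 × 0.25 × 0.75 / 0.5 = 18.75. On 6 df this rejects in 92.3% of trials.

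**5. Results.** The low end is autoregressive ρ = 0.3; the high end is exchangeable ρ = 0.7.

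| Shared fall | Aim 1: λ | Aim 1: joint test rejects | Aim 2: λ | Aim 2: joint test rejects | Interaction only |
|---|---|---|---|---|---|
| 0 | 0 | 5% | 0 | 5% | 5% |
| 0.25 SD | 2.73 to 7.81 | 19% to 52% | 3.09 to 9.26 | 14% to 41% | 5% |
| 0.5 SD | 10.91 to 31.25 | 69% to 99.5% | 12.34 to 37.04 | 55% to 99% | 5% |

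**6. Simulation check (aim 1).** 1,000 trials per scenario, 25 per arm, autoregressive ρ = 0.5, maximum-likelihood likelihood ratio test. The joint test rejected in 5.2%, 25.8% and 81.3% for falls of 0, 0.25 and 0.5 SD (formula: 5.0%, 23.6%, 80.9%). Interaction only rejected in 5.8%, 6.0% and 6.4%. A further simulation with 37 participants, an assumed 20/17 split and exchangeable ρ = 0.5 put interaction only at 6.7%-7.7%. That excess over 5% comes from the chi-square reference in small samples. Aim 2 was computed by formula, not simulated.

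**7. Is a shared fall of this size plausible for the ISI?** For a normal score selected at or above 10, the expected fall on retest is (1 − r) × SD × φ(z)/[1 − Φ(z)], with z = (10 − mean)/SD. With assumed unselected mean 7 to 13, SD 4 to 5 and retest correlation r of 0.5 to 0.7:
- smallest (mean 13, SD 4, r = 0.7): 0.3 × 4 × 0.389 = 0.5 points;
- largest (mean 7, SD 5, r = 0.5): 0.5 × 5 × 1.215 = 3.0 points.

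At SD 4, falls of 0.25 and 0.5 SD are 1 and 2 points, which lie inside that range.

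**The case against.** The strongest reply is that little depends on 1.1a and 2.2a. The primary time points are weeks 6, 12 and 28, the power calculation rests on week 28, and 1.1b-d and 2.2b-d compare the arms at exactly those visits. A shared time effect does not bias those contrasts. The article also presents a feasibility study that puts estimation first. All of this stands and limits the harm. It does not repair 1.1a and 2.2a, which are listed among the primary analyses with no other test, and a joint test gives no between-arm effect size.

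The wording might be a slip for an interaction-only test. But both aims name time alongside group-by-time, so the joint reading is the natural one. Nor is this a detail left to a fuller document: the article states the test.

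Two stronger readings do not hold.

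- A reader might infer that the plan itself expects spontaneous improvement. The Discussion mentions it only as a possible reason why waitlist participants might skip follow-up. The case for a shared fall rests mainly on the entry threshold, and so on the ISI.
- A reader might infer from "mixed effects linear model with autoregressive error structure" and "The model will also include a random slope" that the covariance is also misspecified. The article does not say that a random intercept is absent, nor whether the lag runs by visit or by week. An article may leave both to the full plan.

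**Conclusion.** As written, the test named for 1.1a and 2.2a does not test the relative hypothesis. This follows from the wording alone: any nonzero shared change pushes the joint test above 5% when CBT-I has no effect.

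The size depends on the assumptions listed. With 25 per arm and correlation 0.3 to 0.7, false rejection runs from about one trial in five to one in two (aim 1), or one in seven to two in five (aim 2), for a shared fall of 0.25 SD. For 0.5 SD it is the majority of trials in both aims. The aim 2 figures take the nine listed visits at face value. That model names the BDI-II, which Secondary Outcomes schedules at weeks 0, 12, 28 and 56; fewer visits would change the degrees of freedom and the percentages but not the defect.

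A reader might go further and conclude that the primary analyses as a whole are invalid. The documents do not support that: the fault is confined to one hypothesis in each aim, and the visit-specific contrasts and the planned sample size are untouched.

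**What to change.** For 1.1a and 2.2a, test the group-by-time coefficients only: 3 df for aim 1 and 8 df for aim 2 if time is a factor with the visits listed. Keep group and time in both the full and the reduced model. Report the between-arm contrasts at weeks 6, 12 and 28 with confidence intervals beside the test, in line with the stated emphasis on estimation. A small-sample correction to the likelihood ratio test is optional; the excess it would remove is about 1 to 3 percentage points.

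The cost is a sentence in each aim and a change to the reduced model in the code. No extra data or participants are needed. The Trial Status and Timeline section says that the primary hypotheses had not yet been tested in full, so the change could still be made and documented before the 28-week analysis.
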